**Methods:**

DiNOVasc-COVID-19 is a double-blind, randomised, single-centre, placebo-controlled clinical trial. A total of 98 healthy volunteers (49 males and 49 females) will be recruited. Participants will be randomised into 1 of 2 sub-studies: *part A* or *part B*. *Part A* will investigate the effects of sex on vascular and inflammatory responses to the COVID-19 vaccine. *Part B* will investigate the effects of sex and dietary inorganic nitrate on vascular and inflammatory responses to the COVID-19 vaccine. In *part B*, participants will be randomised to receive 3 days of either nitrate-containing beetroot juice (intervention) or nitrate-deplete beetroot juice (placebo). The primary outcome for both sub-studies is a comparison of the change in flow-mediated dilatation (FMD) from baseline after COVID-19 vaccination. The study has a power of > 80% to assess the primary endpoint. Secondary endpoints include change from baseline in inflammatory and leukocyte counts and in pulse wave analysis (PWA) and pulse wave velocity (PWV) following the COVID-19 vaccination.

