### Original hypothesis

We hypothesise that the COVID-19 vaccine will induce inflammatory responses and thus endothelial dysfunction. However, we expect women to be protected against vascular dysfunction and hypothesise that dietary inorganic nitrate will attenuate the consequent vascular dysfunction following the delivery of the COVID-19 vaccine.

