**Fig. 2 Fig2:**
[figure not shown]
SPIRIT figure. Summary SPIRIT figure showing the visit structure and events during the clinical study

*Part A:* 15 men and 15 women will be randomised into *part A*. This part of the study will recruit equal numbers of men and women to compare the influence of biological sex on inflammatory responses and vascular function following the COVID-19 vaccine.

*Part B*: 34 men and 34 women will be randomised into *part B*. In this study, we will recruit equal numbers of men and women and make comparisons of the effects of dietary inorganic nitrate and sex on vascular function and inflammatory responses. After randomisation into *part B*, participants will undergo further randomisation to receive either 70 mL of a nitrate-containing beetroot juice (5–6 mmol, James White Drinks Ltd., UK, Beet It^®^ Sport Nitrate 400 Shot) or nitrate-deplete placebo control.

Baseline measurements of BP, PWA, PWV, FMD, blood, urine, and saliva will be taken at *visit 2*. Participants randomised to *part B* will begin taking a daily dose of the beetroot juice 2 days before receiving their COVID-19 vaccination and consume 3 consecutive daily doses. The last dose will be taken on the morning of the vaccine. All participants will receive their COVID-19 vaccination on the morning of *visit 3* and return to the clinical research facility to undergo repeat measurements of BP, PWA, PWV, FMD, blood, urine, and saliva 8 ± 2 h after the vaccine. *Visit 4* will occur 28 ± 1 days after delivery of the vaccine, at which point participants will be asked to complete a bespoke experience questionnaire. This questionnaire is bespoke and has been tailored to capture specific aspects of symptoms before and after the COVID-19 vaccination and scored from 0 to 10. These include general health, anxiety and stress, fatigue, and muscle/joint pain. We have also incorporated a rating on the experience of the intervention/placebo and included yes/no questions for whether the juice intervention/placebo was easily incorporated into their daily routine and whether the participant would be keen to continue the intervention as a lifestyle measure if found to be beneficial.

Patients will be recruited throughout all waves of the COVID-19 pandemic. Timing of when COVID-19 vaccination and previous COVID-19 infection will be obtained, to permit exploratory analyses of differences between COVID-19 waves and/or the presence of previous COVID-19 infections.

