### Sample size determination and statistical analysis

In this study, we aim to recruit 98 participants, with 30 healthy volunteers in *part A* and 64 in *part B*. This sample size will empower the study to test the primary endpoint.

These numbers have been based upon our previous experience with typhoid vaccination which causes a reduction in FMD of ~ 1.5% absolute units which is a reduction of approximately 25% of the response [28]. We have previously identified sex differences in the response to typhoid vaccine, with a change from baseline of FMD of − 0.5 (SD = 2.4) in men and 2.4 (SD = 2.5) in women [29]. For *part A*, using these data, if we use a conservative effect size of 25% less than that achieved in our previously published study, 13 participants are required in each group to provide 90% power for the primary outcome. To account for potential dropouts of ~ 10%, 15 participants will be recruited into each group and thus 30 volunteers in total. For the analysis of *part A*, a linear regression model will be used to compare changes in vascular dysfunction pre- to post-vaccination between the sexes, unadjusted and adjusted for important risk factors including age, body mass index, and baseline vessel diameter.

Our unpublished preliminary data investigating the effects of dietary inorganic nitrate on vascular responses (FMD) has identified a decrease in FMD from baseline of 1.4 (SD = 1.5) with typhoid vaccine and with dietary nitrate intervention only 0.08 (SD = 1.7) [20]. Based on these data, for the primary outcome of change in FMD, 25 participants will be required in each group at an 80% power, to observe a difference between the intervention arms. To observe the differences between the sexes, 30 in each group provides a 90% power, which will also offer a > 95% power to detect a rise in [NO_2_^−^], as observed in previous studies [30]. To account for potential dropouts of ~ 10%, a total of 68 volunteers will be recruited. For the statistical analysis in *part B*, analysis of covariance (ANCOVA) will be used to compare the change in vascular dysfunction pre- to post-vaccination, between dietary nitrate and placebo control groups adjusting for pre-vaccination level, and to compare the change in plasma [NO_2_^−^] between the dietary nitrate and placebo control groups.

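### Part B is described and powered as a comparison of the sexes as well as of nitrate, but its only stated model has no sex term

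*Protocol article*

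**What the plan says.** The abstract (Methods) says that Part B "will investigate the effects of sex and dietary inorganic nitrate on vascular and inflammatory responses to the COVID-19 vaccine". The Part B paragraph of Study design and intervention fixes 34 men and 34 women, in order to "make comparisons of the effects of dietary inorganic nitrate and sex on vascular function and inflammatory responses".

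Sample size determination and statistical analysis gives two power statements for Part B. For nitrate, "25 participants will be required in each group at an 80% power, to observe a difference between the intervention arms", based on a "decrease in FMD from baseline of 1.4 (SD = 1.5) with typhoid vaccine and with dietary nitrate intervention only 0.08 (SD = 1.7"). For sex, "To observe the differences between the sexes, 30 in each group provides a 90% power".

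The same section states one Part B analysis: an ANCOVA of pre- to post-vaccination change "between dietary nitrate and placebo control groups adjusting for pre-vaccination level", with the same arm comparison for plasma nitrite. Sex does not appear in it. For Part A, by contrast, the section names a linear regression between the sexes and lists its covariates.

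Under Primary endpoints, Part B names nitrate versus placebo only. Under Randomisation and blinding process, the juice allocation is 1:1 in blocks, and the text does not say whether the blocks are stratified by sex.

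**The concern.** Part B has a power statement for the sexes with no stated Part B analysis to which it belongs. The mismatch matters because the sex figure, not the nitrate figure, appears to set the size of Part B.

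The same section also presents sex as strongly related to the outcome. The earlier typhoid-vaccine study gave FMD changes of minus "0.5 (SD = 2.4) in men and 2.4 (SD = 2.5) in women", and the hypothesis says "we expect women to be protected against vascular dysfunction". A known, already recorded prognostic factor left out of the model goes into the residual and widens the interval for the nitrate effect. If the blocks are not stratified by sex, a chance imbalance between the juice arms also moves the estimate with nothing in the model to correct it.

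**Working it through.** **Inputs** (all from Sample size determination and statistical analysis)
- Nitrate effect: 1.4 − 0.08 = 1.32. Pooled SD = √((1.5² + 1.7²)/2) = 1.603. Standardised effect 1.32/1.603 = 0.82.
- Sex effect: 2.4 − (−0.5) = 2.9. Pooled SD = √((2.4² + 2.5²)/2) = 2.45. Standardised effect 2.9/2.45 = 1.18.
- The 25% reduction, stated for Part A: 0.75 × 2.9 = 2.175. Its use for Part B is an assumption.
- Alpha is not stated; two-sided 0.05 is assumed. Powers are for the two-sample t-test, without the gain from baseline adjustment.

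**1. The plan's own figures.**
- Nitrate: 24.2 per arm are needed for 80%, rounded up to 25. Power at 25 is 81.4%, and at 30 it is 88%. The stated figure reproduces.
- Sex: with 2.175 and SD 2.45, 28 per group are needed for 90%. Power at 30 is 92%, or 90.4% if the arm difference is left as noise. The stated figure is consistent with this.
- Total: 30 per sex gives 60/0.9 = 66.7, so 67, against 68 stated. The nitrate requirement alone gives 50/0.9 = 55.6, so 56. The 68 therefore follows from the sex comparison.

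**2. Share of variance due to sex in a 50:50 arm.** Between-sex variance is (difference/2)²; within-sex variance is 2.45² = 6.00.
- Difference 2.9: 1.45² = 2.10; 2.10/(2.10 + 6.00) = 26%.
- Difference 2.175: 1.0875² = 1.18; 1.18/(1.18 + 6.00) = 16%.
- Equivalent gain in sample size, 1/(1 − share): 1.35 and 1.20, that is 35% and 20% more participants, before any allowance for baseline FMD.

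**3. Nitrate power, by what SD 1.603 represents.**

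*(a) It is a within-sex SD.* The SD in a mixed arm is √(1.603² + (difference/2)²).

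| Sex difference | Mixed-arm SD | Power, 25 per arm | Power, 30 per arm |
|---|---|---|---|
| 2.175 | 1.94 | 66% | 74% |
| 2.9 | 2.16 | 56% | 64% |
| Sex in the model | 1.603 | 81% | 88% |

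*(b) It already mixes the sexes.* The stated 81% and 88% stand without a sex term, and adding sex can only help. The within-sex SD would then be √(2.57 − 1.18) = 1.18 for a difference of 2.175, or √(2.57 − 2.10) = 0.68 for 2.9. Both lie well below the 2.4 to 2.5 of the sex data, so the two data sets fit together poorly. The article does not give the sex mix.

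**4. Chance imbalance, only if the allocation ignores sex.** With 34 of 68 participants men and 34 per arm, the hypergeometric chance that the arms differ by 6 or more men (20 versus 14 or worse) is 22.5%. This treats the allocation as one random split; small blocks would change it somewhat. A gap of 6 shifts the unadjusted difference by (6/34) × 2.9 = 0.51 point, which is 39% of 1.32.

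**5. Sex-by-nitrate interaction.** With 15 per cell, the standard error is 1.603 × √(4/15) = 0.83. For an interaction of 1.32, power is about 35%.

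**The case against.** The best counter-argument has four parts.

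First, the Part B primary endpoints are nitrate versus placebo, the aims list sex and nitrate separately, and Part A tests sex with a stated regression. That is right. A reader might infer that the trial has no test of sex at all, but the gap is confined to Part B. Nor does any section promise a sex-by-nitrate test, so its absence is not a fault.

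Second, covariate lists and secondary models are often left to an analysis plan that is not shown. This carries some weight. But the article does name the single Part B covariate, and it gives a Part B power figure for sex in the same section. The mismatch is within the text.

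Third, a reader might infer that the stated Part B power is unsupported. The documents do not bear that out: 25 per arm at 80% reproduces from its own inputs. Putting the SD of 2.45 from the sex data into the nitrate calculation gives 42–47% at 30 per arm without sex, but still only 54% with it. That shortfall comes mainly from exchanging the SD for that of a different data set, not from the missing term. Similarly, the idea that the nitrate effect halves because only men benefit assumes that 1.32 is the effect in men, which the article does not say.

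Fourth, randomisation protects the nitrate comparison from bias with or without a sex term, and baseline FMD may absorb part of the sex effect. Both stand. The correlation with baseline is not given, so the 16–26% describes a model without the planned covariate. The article neither states nor excludes stratification by sex, so the imbalance figure is conditional.

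**Conclusion.** The point holds as an internal mismatch with a modest statistical cost. Part B is described and sized for a comparison of the sexes that its stated analysis does not contain, and a variable with a larger standardised effect than the treatment (1.18 against 0.82 SD) is left out of the primary model.

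The loss is one of precision, not of validity. On the article's figures sex accounts for about 16–26% of the variance before baseline adjustment. This assumes that the typhoid-vaccine sex difference carries over to COVID-19 vaccination, in full or reduced by 25%. Whether the nitrate power falls below its stated value depends on one unreported fact. If the SDs of 1.5 and 1.7 are within-sex, power without a sex term is 56–66% at 25 per arm and 64–74% at 30. If they already mix the sexes, the stated power stands.

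**What to change.** Before unblinding:

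1. Make the Part B primary model FMD change on arm, sex and baseline FMD.
2. Report the sex coefficient from that model, with its 95% CI, as the Part B sex comparison. Say that the 90% power refers to this main effect of sex and not to an interaction.
3. State the sex mix of the preliminary data behind SD 1.5 and 1.7, so that a reader can tell which power figures apply.

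Optionally, report the nitrate effect in men and in women with 95% CIs from an arm-by-sex model. Label it exploratory and give its low power, about 35% for an interaction of 1.32.

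The primary change costs one degree of freedom out of about 60 participants, some rewording, and no new data. The article says that allocation stays blinded until the end of the study, which leaves room to make it.

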### Ethical considerations

The study protocol, participant facing documentation, recruitment and advertising material, and all amendments were submitted by the chief investigator to a Health Research Authority REC (South Central – Oxford C Research Ethics Committee, identification code 21/SC/0154). Written approval from the committee was obtained, as was sponsor approval, prior to initiating recruitment.

### Safety considerations

In *part B*, the intervention is 70 mL of concentrated beetroot juice (both nitrate-replete and placebo manufactured by James White Drinks Ltd., UK). To manufacture the placebo, an anion exchange resin is used. There are no known serious side effects related to consumption of either the intervention or placebo, and the juice is classed as a foodstuff. Recent publications support its use in clinical trials [31–33]. In the unlikely event that a serious adverse event (SAE) occurs, this will be reviewed by the chief investigator. There will be no special criteria for discontinuing or modifying the allocated intervention; however, if a decision to withdraw participants from the study is required, this will be made by the chief investigator and detailed in the final manuscript.

### Safety reporting

Any adverse event (AE) will be recorded in the participants’ case report form (CRF) and reviewed by the chief investigator. All SAEs will be reported to the sponsor (within 24 h) and REC (within 15 days), where in the opinion of the chief investigator, the event was ‘related’ (as a result of trial procedures) or ‘unexpected’ (not an expected occurrence). SAEs will be recorded in the participants’ CRF. Emergency unblinding as a result of an AE or SAE can take place at any time of day, if required.

### Patient and public involvement

The protocol underwent independent review from the local William Harvey Research Institute Peer Review Committee and review by the Queen Mary and Barts Trust Joint Research Management Office (JRMO). In addition, lay persons were invited to comment on the protocol via the NIHR Barts BRC Cardiovascular patient, public advisory group (PPAG). Furthermore, the final study documents, including participant-facing documents, underwent review and interview by the Research Ethics Council (REC) committee that includes lay members.

### Monitoring

The trial will be monitored by a Trial Steering Committee (TSC) to assess safety, feasibility, or any other arising problems. This committee will be composed of 3 independent experts in the field of pharmacology, interventional cardiology, and clinical trials, in addition to the investigators, statistician, data monitor, and a lay individual. The TSC will meet routinely during the study at 1-year intervals and will meet upon recruitment of the final participant and at study closure. The day-to-day running of the study will be conducted by the clinical fellow of the study, in conjunction with a member of the research team (clinical research assistant), both of whom report directly to the chief investigator. Representatives of Barts NIHR Cardiovascular BRC PPAG will be included in the Trial Steering Committee to be involved in oversight of the trial.

### Dissemination

Primary endpoint data analysis will begin immediately after the last study visit of the last participant. The outcomes and results of this trial will be published according to the CONSORT statement. Trial information will be communicated to the general public via the NIHR Barts Cardiovascular BRC ‘Let’s talk hearts’ seminar series. The results will be published and disseminated in peer-reviewed journals and presented at national and international conferences. DiNOVasc-COVID-19 has been registered with ClincalTrials.gov (http://clinicaltrials.gov, identification code NCT04889274).

## Discussion

In this randomised-controlled trial, we aim to assess the role of sex on vascular function and inflammatory cell trafficking in response to the COVID-19 vaccination and whether dietary inorganic nitrate alters this response. This will be the first study investigating the role of sex and inorganic nitrate treatment in COVID-19 vaccine-induced endothelial dysfunction and will offer novel mechanistic insights into the potential for dietary nitrate to be used as a therapy to attenuate endothelial injury and inflammatory cell responses after delivery of the COVID-19 vaccine and as a model of COVID-19 itself.

We envisage that the greatest barrier to the completion of this study will be recruitment in the face of a changing infection landscape and government policy regarding vaccination. Whilst there is little that the study team can do to mitigate against these issues a key aspect of the study is the randomisation of volunteers across all groups to ensure unbiased distribution of consented volunteers. Such an approach should ensure that the basic demographics and type of vaccine taken, the changing landscape of COVID-19 will be evenly distributed across the groups.

## Trial status

The current protocol version, v2.0 (21/06/2021), was amended from v1.0 with the inclusion of participants for their 2nd and booster vaccines. The first participant was recruited and included in the study in May 2021. Ninety-eight participants have undertaken their screening and second (pre-vaccine/baseline) visit. Six participants are awaiting their COVID-19 vaccine. It is expected that the last participant visit will be undertaken before the end of 2023. The SPIRIT checklist is available in Table 1.

**Table 1 Tab1:** SPIRIT checklist. Summary SPIRIT table identifying key components of the study protocol

		**Reporting item**	**Page and line number**	**Reason if not applicable**
**Administrative information**				
Title	#1	Descriptive title identifying the study design, population, interventions, and, if applicable, trial acronym	Page 1, lines 4–6	
Trial registration	#2a	Trial identifier and registry name. If not yet registered, name of intended registry	Page 3, lines 1–3	
Trial registration: data set	#2b	All items from the World Health Organization Trial Registration Data Set	Page 3, line 1–3	
Protocol version	#3	Date and version identifier	Page 17, line 18	
Funding	#4	Sources and types of financial, material, and other support	Page 19, lines 2–5	
Roles and responsibilities: contributorship	#5a	Names, affiliations, and roles of protocol contributors	Page 19, line 7 to age 20 line 2	
Roles and responsibilities: sponsor contact information	#5b	Name and contact information for the trial sponsor	Page 18, lines 3–4	
Roles and responsibilities: sponsor and funder	#5c	Role of study sponsor and funders, if any, in study design; collection, management, analysis, and interpretation of data; writing of the report; and the decision to submit the report for publication, including whether they will have ultimate authority over any of these activities	Page 19, line 7 to page 20 line 2	
Roles and responsibilities: committees	#5d	Composition, roles, and responsibilities of the coordinating centre, steering committee, endpoint adjudication committee, data management team, and other individuals or groups overseeing the trial, if applicable (see Item 21a for data monitoring committee)	Page 16, lines 5–13	
**Introduction**			Page 4, lines 3–24	
Background and rationale	#6a	Description of research question and justification for undertaking the trial, including summary of relevant studies (published and unpublished) examining benefits and harms for each intervention	Page 4, lines 3–24	
Background and rationale: choice of comparators	#6b	Explanation for choice of comparators	Page 5, lines 3–7	
Objectives	#7	Specific objectives or hypotheses	Page 5, lines 9–19	
Trial design	#8	Description of trial design including type of trial (e.g. parallel-group, crossover, factorial, single group), allocation ratio, and framework (e.g. superiority, equivalence, non-inferiority, exploratory)	Page 7, line 18	
**Methods: participants, interventions, and outcomes**				
Study setting	#9	Description of study settings (e.g. community clinic, academic hospital) and list of countries where data will be collected. Reference to where list of study sites can be obtained	Page 5, lines 10–13; page 8, lines 2–3	
Eligibility criteria	#10	Inclusion and exclusion criteria for participants. If applicable, eligibility criteria for study centres and individuals who will perform the interventions (e.g. surgeons, psychotherapists)	Page 6, line 19 to page 7, line 15	
Interventions: description	#11a	Interventions for each group with sufficient detail to allow replication, including how and when they will be administered	Page 8, lines 16–19	
Interventions: modifications	#11b	Criteria for discontinuing or modifying allocated interventions for a given trial participant (e.g. drug dose change in response to harms, participant request, or improving/worsening disease)	Page 15, lines 2–10	
Interventions: adherance	#11c	Strategies to improve adherence to intervention protocols, and any procedures for monitoring adherence (e.g. drug tablet return; laboratory tests)	Page 11, line 11 to page 12, line 7	
Interventions: concomitant care	#11d	Relevant concomitant care and interventions that are permitted or prohibited during the trial	Page 8, lines 2–9	
Outcomes	#12	Primary, secondary, and other outcomes, including the specific measurement variable (e.g. systolic blood pressure), analysis metric (e.g. change from baseline, final value, time to event), method of aggregation (e.g. median, proportion), and time point for each outcome. Explanation of the clinical relevance of chosen efficacy and harm outcomes is strongly recommended	Page 10, line 12 to page 12, line 17	
Participant timeline	#13	Time schedule of enrolment, interventions (including any run-ins and washouts), assessments, and visits for participants. A schematic diagram is highly recommended (see figure)	Page 10, lines 5–6	
Sample size	#14	Estimated number of participants needed to achieve study objectives and how it was determined, including clinical and statistical assumptions supporting any sample size calculations	Page 13, line 5 to page 14, line 16	
Recruitment	#15	Strategies for achieving adequate participant enrolment to reach target sample size	Page 5, lines 10–13; page 17, lines 9–15	
